## Abstract

**Background:**

Gastro-intestinal (GI) intolerance is a frequently reported outcome in patients with kidney failure receiving maintenance dialysis and those who have received kidney transplants. Symptoms of GI intolerance (diarrhoea, constipation, bloating, abdominal pain, heart burn, and reflux) are associated with significant reduction in quality of life, morbidity, and increased used of healthcare resources. Having chronic kidney disease (CKD), together with related changes in diet and medication, may alter the gut microbiota and the microbial-derived uraemic metabolites that accumulate in kidney failure, and contribute to various complications including chronic diarrhoea, opportunistic infections, and drug-related colitis. Despite the high disease burden among patients with kidney replacement therapies, GI symptoms are often under-recognised and, consequently limited resources and strategies are devoted to the management of gastrointestinal complications in patients with CKD.

**Methods:**

The CKD Bowel Health Study is a multi-centre mixed-methods observational longitudinal study to better understand the bowel health and GI symptom management in patients with CKD. The program comprises of a longitudinal study that will assess the burden and risk factors of GI intolerance in patients treated with maintenance dialysis; a semi-structured interview study that will describe experiences of GI intolerance (including symptoms, treatment, self-management) in transplant candidates and recipients; and a discrete choice experience to elicit patient preferences regarding their experiences and perspectives of various intervention strategies for the management of GI symptoms after kidney transplantation.

**Discussion:**

This proposed program of work aims to define the burden the GI intolerance in patients with kidney failure and generate evidence on the patients’ experiences of GI intolerance and their perspectives on their clinical and own management strategies of these symptoms, ensuring a patient-centred approach to guide clinical decision making and to inform the best study design for intervention trials.

**Trial registration:**

This study is registered on the Australian New Zealand Clinical Trials Registry (ANZCTR): ACTRN12621000548831. This study has been approved by the Western Sydney Local Health District Human Research Ethics Committee of New South Wales Health (HREC ETH03007). This study is supported by a National Health and Medical Research Council (NHMRC) Australia Investigator Grant (APP1195414), and an NHMRC Australia Postgraduate Scholarship (APP2005244).

## Background

Gastro-intestinal (GI) intolerance is a frequently reported outcome in patients with kidney failure receiving maintenance dialysis and those who have received kidney transplants. Symptoms of GI intolerance (diarrhoea, constipation, bloating, abdominal pain, heart burn, and reflux) are associated with significant reduction in quality of life (in particular anxiety and life participation), substantial morbidity burden, increased used of health care resources, and increased risk of allograft complications (including acute rejection as a result of a reduction in immunosuppression). Prior observational studies reported up to 50% of kidney transplant recipients experience adverse GI side effects from immunosuppression, such as mycophenolate mofetil and tacrolimus. Many patients require dose-reduction of immunosuppressive agents that could predispose to a higher risk of acute rejection [1–6]. Alternative immunosuppressive agents such as enteric-coated mycophenolic acid (EC-MPA, Myfortic®) may be better tolerated, but up to 30% of patients continue to experience symptoms of GI intolerance [7]. Other than dose reduction and/or modification of immunosuppressive regimen, there has been no other proven effective treatment strategies that have been shown to reduce GI intolerance in kidney transplant recipients. In patients treated with maintenance dialysis, the most common symptoms include nausea, vomiting, diarrhoea, constipation, heartburn and reflux. In fact, up to 80% of dialysis patients experience GI intolerance, in particular constipation which is exacerbated by the use of oral phosphate binders [8].

There are many reasons for the observed GI changes and symptoms in kidney disease, but retention of uremic molecules produced by microbial metabolism within the gastrointestinal tract may have played a key role in the clinical syndrome of uraemia and its complications [9]. These microorganisms may be present in higher concentration within the GI tract because of alterations in gut microbiota and colonic flora in patients with advanced stage CKD. In kidney transplant recipients, reduced microbial diversity and reduced relative abundance of commensal bacterial taxa that may be critical in the digestion of complex sugars (e.g., *Ruminococcus, Dorea, Coprococcus,* and *Bacteroides*) may be associated with post-transplant non-infectious diarrhoea [10]. Prior work has also shown that the risk of developing colorectal cancer in patients with CKD is doubled compared to the general population [11, 12]. Factors for the increased risk may include age, male sex, the cumulative dose immunosuppression and disturbances in the gut microbiome [12]. The gut microbiota is not only capable of promoting intestinal homeostasis and antitumor responses but can also contribute to chronic dysregulated inflammation as well as have genotoxic effects that lead to carcinogenesis [13]. Prior work has indicated that microbial dysbiosis, a pathological imbalance in the microbial community, is implicated in the development of colorectal adenomas.

The intestinal microbiota, therefore, represents a new therapeutic target to improve outcomes of CKD including reducing uraemic symptoms and metabolic abnormalities in patients with CKD and kidney failure, delay the progression of CKD, and possibly reduce the development of cancer [10]. Nutritional supplements such as probiotics or synbiotics (the combination of probiotics and prebiotics) which have been shown to modulate the GI ecosystem by reducing harmful effects of bacterial imbalance in the gut, strengthen the immune system, protect the gut barrier, and reduce the detrimental effects of uremic toxins in patients with CKD [12]. As GI disturbances remain a substantial burden for patients with CKD and their caregivers, a greater understanding of how the alteration in microbial diversity contributes to GI intolerance in patients with kidney failure and kidney transplants will inform the most appropriate clinical trial design for novel interventions to address this important patient-centred outcome. This proposed program of work will define the burden of GI intolerance and symptoms in patients with kidney failure on dialysis and with kidney transplants, and understand patients’ experiences of GI intolerance, and their perspectives on the management strategies of these symptoms.

### Research question

To better understand the prevalence, severity and management strategies of GI intolerance in kidney transplant candidates and recipients.

### Objectives

#### Primary objective

To determine the prevalence and risk factors of GI intolerance and symptoms in patients: with kidney failure (dialysis only); before transplant (candidate listed on the transplant waiting list or have a pre-emptive donor); and after kidney transplantation.

#### Secondary objectives

To describe the experiences, symptoms and management strategies of GI intolerance in kidney transplant candidates and transplant recipients.

#### Tertiary objective

To elicit patients’ preferences regarding experiences and perspectives on the management strategies for GI symptoms and intolerance after transplantation.

## Methods

### Study designs

An outline of the three study designs and study procedures is displayed in Fig. 1.An observational longitudinal study of the burden and risk factors of GI intolerance in patients treated with kidney replacement therapyA semi-structured interview study in kidney transplant candidates and kidney transplant recipients.A discrete choice experiment of patient preferences regarding the perspectives of the different treatment and intervention strategies for the management of GI symptoms in patients with kidney transplants.

**Fig. 1 Fig1:**
[figure not shown]
Study Design

This protocol is developed to address the reporting checklists for:STROBE (Strengthening The Reporting of OBservational studies in Epidemiology) for the observational study and discrete choice experience [14];COREQ (COnsolidated criteria for REporting Qualitative research) for the qualitative interviews [15].

This study is registered on the Australian New Zealand Clinical Trials Registry (ANZCTR): ACTRN12621000548831. This study has been approved by the Western Sydney Local Health District Human Research Ethics Committee of New South Wales Health (HREC ETH03007).

### Location & Setting

This multi-centre study will be based at two hospitals in Australia: The Western Renal Service (Western Sydney Local Health District and Nepean Blue Mountains Local Health District), New South Wales, Australia (primary location); and the Renal Medicine and Transplantation Department (Northern Metropolitan Health Service), Sir Charles Gairdner Hospital, Western Australia, Australia (secondary location).

### Consent

We will obtain informed consent from each adult participant, caregiver, or legal guardian. There will be no implied consent. To ensure COVID-19-safe practices, we will allow for video or phone verbal consent. Participants can withdraw their consent for the study at any time without affecting their specialist care or disease management in any way.

### Study population

#### Eligibility criteria

To be eligible for this program of work, participants must be: adults aged 18 years and older, with kidney failure (CKD Stage 4 to 5D: estimated glomerular filtration rate = 0 to 29 mL/min/1.73m^2^ and albuminuria > 300 mg/g) [16], on dialysis only, or on dialysis and listed on the deceased donor kidney transplant waiting list, or patients with kidney failure with a planned pre-emptive transplant within 12 months. The study includes both kidney-only and simultaneous pancreas-kidney transplant candidates of any GFR and a minimum one functioning organ. Participants will be recruited into the study irrespective of whether they had current or past experiences of GI intolerance and symptoms.

#### Exclusion criteria

Prior bowel resection, chronic pancreatic insufficiency, or recent infection-related diarrhoea in the last 3 months. Pre-dialysis patients. Transplant recipients we will exclude recent rejection episodes, and unable to give informed consent.

### Recruitment procedure

All eligible patients will be identified using the renal databases and through communication with the medical and nursing staff of the unit. This will be either via phone recruitment or consecutive patients attending the outpatient clinics. Participant consent forms, clearly and succinctly outline the screening procedure and the associated harms will be given to all eligible patients to read through at the face-to-face recruitment by the research staff. Informed consent was written where possible and to ensure COVID-19-safe practices, we will allow for video or phone verbal consent as approved by the ethics committee. For patients with non-English speaking background, a qualified health care interpreter will translate information sheets into the patient’s native language. Participation in the study is entirely voluntary. Patients are in no way obliged to participate and if they do, they can withdraw anytime from the study, with their care unaffected in any way.

#### Longitudinal cohort study

Recruitment of participants will occur anytime pre-transplant and the following will be collected (Table 1):General patient contact information, demographic characteristics, medical history, and CKD health status via the Observational Questionnaire (Baseline).The baseline assessments, pre-transplant of observational data via the Observational Questionnaire (Baseline) which will collect transplant status, current medications and supplements, general health via the EQ-5D Questionnaire [17], faecal characteristics using the Bristol Stool Chart [18], gastrointestinal symptoms via the Gastrointestinal Symptom Rating Scale (GSRS) [19, 20], quality of life using the Gastrointestinal Quality of Life Scale (GIQLS) [21], personal management strategies of gut health and GI symptoms, dietary patterns using the Food Frequency Questionnaire [22], and safety parameters and adverse events.To repeat the instruments, the Observational Questionnaire (Follow-Up) will be administered at 4-, 12-, and 28-weeks post-transplant (28 weeks being the final follow-up time-points). This questionnaire contains the same instruments without the patient contact information and demographic sections.

**Table 1 Tab1:** Study Visit Schedule

Task	Time points				
	Visit 1		Visit 2	Visit 3	Visit 4
	Recruitment and baseline (anytime pre-Tx)	Tx	4 wk. post-Tx	12 wk. post-Tx	28 wk. post-Tx
**Screening** against eligibility criteria	✓				
**Participant Information Consent Form:** Combined form for all 3 study arms	✓				
**Questionnaire (baseline)**	✓				
**Questionnaire (follow-up)**			✓	✓	✓
**Qualitative Interview**	✓				✓
**Discrete Choice Experiment Survey**				✓	
**Tx:** transplant; **wk:** weeks.					

The primary outcomes are: (1) prevalence of GI intolerance (any severity) in patients with kidney failure and kidney transplants; and (2) change in GI symptom burden before and after transplantation. Secondary outcomes are: (1) risk factors of GI intolerance; (2) stool characteristics; (3) general health status, and (4) quality of life.

Instruments: the observational questionnaires (baseline and follow-up) will collect a broad range of both clinically important and patient-reported outcomes [23] using a variety of validated instruments. The EQ-5D tool is a 5-question Likert scale for measuring general health status according to activities of daily living [17]. The Bristol Stool Chart is a 7-point illustrative scale for identifying different categories of stool characteristics [18]. The GSRS instrument comprises of 15 items combined into five symptom-domains of reflux, abdominal pain, indigestion, diarrhoea and constipation. The GSRS is a graded scale, with a score of 1 representing the absence of any GI symptoms, whereas a score of 7 representing severe GI symptoms [19–21]. The Food Frequency Questionnaire is a validated 131-item dietary assessment tool to capture a patient’s content, frequency, and portion sizes of food and beverages over a specified time period, ranging from 1 to 12 months depending on the question [22].

Statistical analysis: we will undertake a descriptive analysis of the prevalence and management strategies of GI intolerance in patients with kidney failure and have a kidney transplant. Baseline characteristics and dietary patterns will be compared between recipients with and without GI intolerance using chi-square (to compare categorical variables), analysis of variance (compare means for normally distributed variables) and Kruskal-Wallis tests (to compare medians for non-normally distributed variables). Longitudinal mixed models with random intercepts will be conducted to assess the relationship between dietary patterns and GI intolerance, accounting for confounders including age, sex, medication use, and CKD stage.

*Sample size calculation*: If the true prevalence of GI intolerance and symptoms is 7–10% in patients with kidney failure, a sample size of 100 will ensure 95% certainty that the prevalence measure in this sample between 5 to 15%, where n = minimum sample, p = estimated prevalence, q = 100-p, E = 5 (margin of sampling error) $$n= pq/{\left(\frac{E}{1.96}\right)}^2$$ [24].

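### The stated comparison by GI-intolerance status is limited to recipients, so non-dietary risk factors have no stated comparison in enrolled patients who are not transplanted, although the objective covers them

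*Protocol article*

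**What the plan says.** The Primary objective of the protocol article covers three populations: "To determine the prevalence and risk factors of GI intolerance and symptoms in patients: with kidney failure (dialysis only); before transplant" (listed, or with a pre-emptive donor), and after transplantation. The Methods part of the Abstract describes "a longitudinal study that will assess the burden and risk factors of GI intolerance in patients treated with maintenance dialysis". Under Longitudinal cohort study, risk factors of GI intolerance are the first secondary outcome, with no limit on population.

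The Statistical analysis paragraph of the same section contains three elements:

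- a descriptive analysis of prevalence and management, covering both kidney failure and transplant;
- a group comparison, in which baseline characteristics and diet are to be "compared between recipients with and without GI intolerance using chi-square (to compare categorical variables", with analysis of variance or Kruskal-Wallis tests for the other variables;
- a model: "Longitudinal mixed models with random intercepts will be conducted to assess the relationship between dietary patterns and GI intolerance, accounting for confounders", the confounders being age, sex, medication use and CKD stage.

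Participants are recruited at any time before transplant. All complete the baseline questionnaire, which covers demographics, history, medication, GI symptoms (GSRS) and diet. The three follow-up questionnaires, at 4, 12 and 28 weeks, all fall after transplant. Eligibility admits patients who are on dialysis only.

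**The concern.** The group comparison is the only stated analysis that sets a range of characteristics against GI-intolerance status, and its stated population is narrower than the objective's. A dialysis-only participant, or a listed participant who is not transplanted during the study, falls outside it. For these people Visit 1 is the only source of data, and the comparison does not use it.

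At stake is part of a stated objective. The Background quotes its highest burden, up to 80%, for dialysis patients, and names oral phosphate binders as aggravating constipation in them. That is a non-dietary factor for which no comparison among untransplanted patients is stated. A later analysis plan that followed the sentence literally would carry the restriction forward.

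**Working it through.** **Step 1. What *recipients* means.** The Research question, the Secondary objectives and the interview study under Study designs set transplant candidates against recipients. The Background uses the word for transplanted patients. Where the article means the wider cohort it has other terms: the Study designs section speaks of patients treated with kidney replacement therapy, and the sentence just before the group comparison refers to patients with kidney failure. Transplant recipients is therefore the natural reading, though not the only possible one.

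**Step 2. Objective against stated analyses.**

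| Population | Prevalence | Diet and GI intolerance | Other characteristics and GI intolerance |
|---|---|---|---|
| Dialysis only | Descriptive | Mixed model, pooled | None stated |
| Listed or pre-emptive, not transplanted in the study | Descriptive | Mixed model, pooled | None stated |
| Transplanted | Descriptive | Mixed model and group comparison | Group comparison |

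The mixed model is not restricted to recipients, so a patient who is never transplanted can enter it, but with one record. Its exposure is dietary pattern. Age, sex, medication use and CKD stage enter as confounders, not as candidate risk factors, and no estimate by population is stated.

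**Step 3. The plan's own sample size.** The formula is n = p(100 − p)/(E/1.96)², with E = 5, so (5/1.96)² = 6.508.

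- p = 7: 7 × 93/6.508 = 100.04, which reproduces the stated 100.
- p = 10: 10 × 90/6.508 = 138.3, which does not.

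The 100 is a precision figure for a single prevalence at the low end of the assumed range. No effect size or power is stated for any risk-factor comparison, so there is no planned power to reproduce.

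**Step 4. Cases available.** Cases = number analysed × prevalence. The number transplanted is not in the document; 30, 50 and 70 of 100 are assumptions. The prevalences are the 7–10% of the sample size paragraph and, as an alternative range, the Background figures of up to 50% (transplant) and up to 80% (dialysis).

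| Patients compared | 7% | 10% | 50% | 80% |
|---|---|---|---|---|
| 30 recipients | 2.1 | 3.0 | 15 | 24 |
| 50 recipients | 3.5 | 5.0 | 25 | 40 |
| 70 recipients | 4.9 | 7.0 | 35 | 56 |
| All 100 at Visit 1 | 7.0 | 10.0 | 50 | 80 |

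At 80% the non-cases are the scarce group: 30 × 0.2 = 6 and 70 × 0.2 = 14 among recipients, against 100 × 0.2 = 20 in all.

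**Step 5. What the wider comparison can and cannot do.** Take as an illustration a factor present in 70% of cases and 40% of non-cases (assumption), tested two-sided at 5%. At 7–10% prevalence the approximate power is 12–15% with 30 recipients, 24–32% with 70, and 33–44% with all 100. The normal approximation is rough at these counts. Any single population within the 100 would do worse.

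**The case against.** The case against rests on five arguments.

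- **The word may be loose.** No cohort participant has had the study transplant at baseline, yet the sentence compares baseline characteristics of *recipients*. It may simply mean participants. The restriction may therefore be unintended, but the sentence then still needs correcting.
- **Diet is a risk factor, and the mixed model is open to everyone.** This stands. A reader might infer that dialysis-only and listed patients get no risk-factor answer, or contribute nothing. The article does not support that: their Visit 1 diet and symptom records can enter the model, and adjustment for CKD stage is consistent with including them.
- **Recipients' own baseline data are pre-transplant.** This also stands. The listed group is not wholly left out, and the article does not say at which visit GI intolerance is classified for the comparison. The gap is firmest for dialysis-only patients and others not transplanted during the study.
- **Risk factors are ranked as a secondary outcome.** True, although the Primary objective includes them. The two places differ, so it is too simple to call this an unmet primary aim.
- **An article leaves analysis sets to a fuller document.** That would answer an omission. Here the article names a population, and it does not match the objective.

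**Conclusion.** The mismatch holds in a limited form. As written, non-dietary risk factors have no stated comparison in enrolled patients who are not transplanted, and diet has only a pooled model answer for them, although their baseline data are collected. This rests on reading *recipients* as transplant recipients, which is how the article uses the word elsewhere.

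The size depends on the unstated number transplanted. With 30 to 70 of 100 (assumption), recipients give about 2 to 7 cases against 7 to 10 in all 100 at 7–10% prevalence, or about 15 to 56 against 50 to 80 at 50–80%.

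A reader might go further and infer that the study cannot report risk factors on dialysis at all, or that using all 100 would give a well-powered analysis. Neither is supported. The data exist and the mixed model is unrestricted. High power for all 100 appears only under an assumed large effect and a prevalence far above the planned 7–10%, and it would describe the pooled sample, not dialysis-only patients. The main loss is coverage of the objective, not power.

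**What to change.** Change the analysis population in the Statistical analysis paragraph:

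1. Compare participants with and without GI intolerance at Visit 1 in all those enrolled. Alternatively, regress the baseline GSRS score on a small set of characteristics; a continuous outcome suits 100 patients better than a handful of cases.
2. Include treatment group (dialysis only, listed, pre-emptive) as a term, and also report estimates by group, descriptively where numbers are small. A main-effect term alone would not show risk factors within dialysis-only patients.
3. Keep the comparison among recipients as a separate post-transplant analysis, and say at which visit GI intolerance is classified.

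If *recipients* was meant as participants, correcting the word and adding the results by group is enough.

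The cost is one extra analysis and revised wording. No new data are needed. Group-specific estimates will be imprecise and should be presented as such.

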#### Semi-structured interview study

##### Participant recruitment and selection

Participants who were identified as eligible for the observational longitudinal study at recruitment (anytime pre-transplant), and who reported the presence of GI symptoms, burden and intolerance, will be invited to participate in the qualitative semi-structured interviews. This will be a longitudinal qualitative study and purposive sampling will be used to ensure a broad range of demographics are included in this study. We plan to enrol a minimum of 30 CKD patients from this study population until saturation. Participants will be interviewed twice: once at baseline (anytime pre-transplant) (Visit 1, Table 1) and once post-transplant at the 28-week follow-up (Visit 4, Table 1).

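### The sample size assumes 7–10% prevalence with a ±5-point margin, which conflicts with the Background's figure of up to 80% on dialysis; at 20–80% prevalence, 100 participants give about ±8 to ±10 points

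*Protocol article*

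**What the plan says.** The sample size paragraph in the Longitudinal cohort study section starts from "If the true prevalence of GI intolerance and symptoms is 7–10% in patients with kidney failure". It concludes that "a sample size of 100 will ensure 95% certainty that the prevalence measure in this sample between 5 to 15" percent. The formula is n = pq/(E/1.96)², with p in percent, q = 100 − p and "E = 5 (margin of sampling error").

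Three other places bear on the assumed prevalence:

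- **Background, dialysis:** "up to 80% of dialysis patients experience GI intolerance". For transplant recipients the same section reports "up to 50% of kidney transplant recipients experience adverse GI side effects from immunosuppression", and up to 30% with continuing symptoms on an alternative agent.
- **Primary outcome (1), Longitudinal cohort study:** "prevalence of GI intolerance (any severity) in patients with kidney failure and kidney transplants".
- **Semi-structured interview study, Participant recruitment and selection:** symptomatic patients eligible for the cohort are invited, and "We plan to enrol a minimum of 30 CKD patients from this study population until saturation".

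**The concern.** The assumed prevalence and the dialysis figure in the Background describe the same condition in an overlapping population, since the cohort enrols dialysis patients. One is 7–10% and the other is as high as 80%. The article does not say that a narrower definition was used for sizing; the sample size sentence speaks broadly of intolerance and symptoms, and the primary outcome includes any severity. The interview plan also suggests that more symptomatic patients were expected than the 7 to 10 per 100 implied by the sizing assumption.

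This matters because the variance of a proportion rises steeply between 7% and 50%. A low planning value therefore makes the margin look smaller than it will be at a higher prevalence. The paragraph is the only sample size justification for the longitudinal cohort and it supports a primary outcome, so readers would expect a precision that the design may not deliver.

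**Working it through.** **Inputs.** p = 7–10%, n = 100, E = 5 points and z = 1.96 come from the sample size paragraph. Prevalences of 30%, 50% and 80% are the Background's upper values. The values 15% and 20% are added here to show what happens below those ceilings.

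**Step 1: reproduce the stated n.** The denominator is (5/1.96)² = 6.508.

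- p = 7%: 7 × 93 / 6.508 = 651 / 6.508 = 100.04. This matches the stated 100.
- p = 10%: 10 × 90 / 6.508 = 900 / 6.508 = 138.3, rounded up to 139. This does not match.

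So 100 follows from the lower end of the stated range only.

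**Step 2: margin at n = 100.** Reversing the formula gives E = 1.96 × √(pq/100).

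| Prevalence | pq | Margin at n = 100 | n needed for ±5 |
|---|---|---|---|
| 7% | 651 | ±5.0 | 101 (100.04 rounded up) |
| 10% | 900 | ±5.9 | 139 |
| 15% | 1275 | ±7.0 | 196 |
| 20% | 1600 | ±7.8 | 246 |
| 30% | 2100 | ±9.0 | 323 |
| 50% | 2500 | ±9.8 | 385 |
| 80% | 1600 | ±7.8 | 246 |

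Because pq is symmetric about 50%, every prevalence from 20% to 80% gives a margin between ±7.8 and ±9.8. Wilson intervals agree: half-widths of 7.8 points at 80% and 9.6 at 50%.

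**Step 3: the 5–15% statement.** This interval equals p ± 5 only for p = 10%; for p = 7% it would be 2–12%. The two parts of the calculation therefore use different ends of the range. The exact binomial probability that the sample prevalence of 100 participants lies between 5% and 15% is:

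- 84% at a true prevalence of 7%
- 94% at 10%
- 13% at 20%
- 0.04% at 30%
- effectively zero at 50% or 80%

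Neither end of the protocol's own range reaches the stated 95%.

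**The case against.** The strongest reply is that the Background gives ceilings, not estimates. Each figure is an upper value with no lower bound, so a prevalence well below 30% is compatible with it. This stands. A reader might infer that the true margin is known to be ±8 to ±10; the documents do not support that, and the range is conditional on a prevalence of 20–80%. The direction does not depend on it, because the margin passes ±5 as soon as prevalence exceeds about 7%.

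Second, the 50% figure is not like for like. It concerns side effects of immunosuppression in recipients, whereas the sizing sentence is about kidney failure. This also stands: the direct conflict is with the dialysis figure. The transplant figure is relevant only because the primary outcome covers recipients as well.

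Third, a reader might divide the 100 into dialysis, pre-transplant and post-transplant groups and expect much wider margins for each. The article gives no group sizes, and it follows participants recruited before transplant through to 28 weeks after it, so the pre- and post-transplant estimates share people. No separate subgroup margins can be derived.

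Fourth, a reader might infer that 30 symptomatic interviewees are practically impossible at 7–10%. That would require a closed pool of exactly 100. Interviewees are drawn from patients eligible for the cohort, sampling runs until saturation, and the formula calls n a minimum. The interview target is only an indication that a higher prevalence was expected.

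Finally, the analysis of prevalence is descriptive, and ±8 to ±10 points may be adequate for a study of burden. That supports keeping the sample size. It does not support the stated ±5.

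**Conclusion.** The point holds as a conflict between a stated input and the protocol's own evidence. The assumption of 7–10% in kidney failure is not reconciled with up to 80% on dialysis or with an any-severity primary outcome. The precision claim also fails within its own terms: 100 gives ±5 at about 7%, but ±5.9 at 10%. If prevalence lies anywhere from 20% to 80%, the 95% margin is ±7.8 to ±9.8, roughly 1.6 to 2 times the stated one (7.8/5 = 1.56; 9.8/5 = 1.96).

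These margins assume simple binomial sampling and that all 100 contribute. The post-transplant estimate will be less precise if fewer than 100 are transplanted and followed. The documents do not show that 100 is too few for the study's purpose, only that the precision attached to it is wrong.

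**What to change.** Rewrite the sample size paragraph:

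1. Replace 7–10% with a range consistent with the Background, for example 20–80%, labelled as an assumption because the Background figures are upper values.
2. State the 95% margin at n = 100 as about ±8 to ±10 points, and delete the 5–15% statement.
3. Note that the post-transplant estimate will have a wider margin if fewer than 100 participants are transplanted and followed.
4. If 7–10% was meant for a narrower definition of GI intolerance, state that definition and give the precision for the any-severity outcome separately. The primary outcome itself should stay as it is; it should not be altered to suit the calculation.

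Keep n = 100. The cost is the rewording of one paragraph and a less favourable stated precision.

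### The precision claimed for 100 participants does not follow from the protocol's own formula: 100 is the answer at 7% prevalence, while the 5–15% range belongs to 10%, which needs 139

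*Protocol article*

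**What the plan says.** The calculation is in the protocol article, Longitudinal cohort study, under the sample size heading. It starts from an assumed range: "If the true prevalence of GI intolerance and symptoms is 7–10% in patients with kidney failure". From this it concludes that "a sample size of 100 will ensure 95% certainty that the prevalence measure in this sample between 5 to 15" percent.

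The formula is printed beside the claim: n = pq/(E/1.96)², on the percentage scale, with "p = estimated prevalence, q = 100-p" and "E = 5 (margin of sampling error"). The text does not say which prevalence between 7% and 10% produced the figure of 100.

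The quantity being sized is the first primary outcome in the same section: "prevalence of GI intolerance (any severity) in patients with kidney failure and kidney transplants".

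**The concern.** Inputs, formula and result are all printed, so the claim can be checked without outside information. It makes four statements at once: n = 100, 95% certainty, an observed prevalence of 5–15%, and a true prevalence of 7–10%. A range of 5–15% is centred on 10%, so with a 5-point margin it can only be the interval for the top of the assumed range. The required n rises with prevalence over this range, so the top of the range should also set the sample size. The figure of 100 looks too small for that.

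This paragraph is the only justification given for the size of the cohort and the only statement of how precisely the first primary outcome will be estimated. If it is wrong, readers are promised a precision that the design lacks even under its own assumption.

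**Working it through.** **Inputs**, all from the sample size paragraph: p = 7% to 10%; q = 100 − p; E = 5 points; multiplier 1.96; n = 100; claimed range 5–15%; claimed certainty 95%.

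**Step 1: reproduce the protocol's 100.** (5/1.96)² = 6.5077, so n = pq/6.5077.

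At p = 7%: 7 × 93 = 651, and 651/6.5077 = 100.04. This is the source of 100 (strictly 101 if rounded up). The interval that goes with it is 7 ± 5, or 2–12%.

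**Step 2: find the n that belongs to 5–15%.** That range is 10 ± 5, so p = 10%: 10 × 90 = 900, and 900/6.5077 = 138.3, rounded up to 139.

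**Step 3: turn the formula round.** With n = 100 the half-width is 1.96 × √(pq/100). The last column is the literal reading of the claim: the exact binomial probability that between 5 and 15 of 100 participants are affected.

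| True prevalence | n for ±5 points | Half-width at n = 100 | Interval at n = 100 | P(observed 5–15%) at n = 100 |
|---|---|---|---|---|
| 7% | 100.04 | 5.00 | 2.0–12.0% | 83.5% |
| 8% | 113.1 | 5.32 | 2.7–13.3% | 90.4% |
| 8.5% | 119.5 | 5.47 | 3.0–14.0% | 92.4% |
| 9% | 125.9 | 5.61 | 3.4–14.6% | 93.6% |
| 10% | 138.3 | 5.88 | 4.1–15.9% | 93.6% |

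A fine scan of prevalence from 7% to 10% puts the maximum of the last column at 94.0%, near 9.5%. No value in the assumed range reaches 95%. With 139 participants and a prevalence of 10%, the probability is 95.2%.

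**Step 4: look for a reading that rescues the sentence.**

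- Exact (Clopper–Pearson) intervals are 2.9–13.9% for 7 of 100 and 4.9–17.6% for 10 of 100. Wilson intervals are 3.4–13.7% and 5.5–17.4%. None of these is 5–15%.
- A multiplier of 1.645 (90% confidence) at p = 10% gives n = 97.4, close to 100. But the protocol prints 1.96 and claims 95%.

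**The case against.** The strongest reply accepts the arithmetic and disputes its weight. The claim sentence lacks a verb, and the formula and margin suggest that the authors meant prevalence ± 5 points rather than one fixed window for every prevalence from 7% to 10%. On that reading, 100 is correct at 7%: the exact probability of an observed value within 5 points of the truth is 97.2%. At 10% it is 93.6%. The shortfall is then at most 0.9 points of half-width, plus a mismatched printed range, and the 83.5% figure depends on the literal reading. The prevalence analysis is descriptive, so no test or power claim rests on the sentence.

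Much of this stands. The loss is small, 100 is reproducible at 7%, and a 5-point margin would also hold below 7%, outside the assumed range. But the kinder reading does not save the text: ±5 points is still missed at every tabulated prevalence above 7%, and 5–15% is still not the interval for the prevalence that gave 100.

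A second reply is that 7–10% is itself doubtful. The Background section of the protocol article reports GI intolerance in up to 80% of dialysis patients and GI side effects of immunosuppression in up to 50% of transplant recipients. By the same formula, 100 participants give ±7.8 points at 80% and ±9.8 points at 50%. This is a fair but separate matter. It means that any corrected sentence must name the prevalence it assumes; it does not make the present sentence right.

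**Conclusion.** The concern holds. The sample size of 100 comes from a prevalence of 7%, whose interval is 2–12%. The printed 5–15% comes from a prevalence of 10%, which needs 139 participants, 39 more than the 100 planned. No prevalence in the protocol's own range satisfies the sentence as a whole.

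The practical effect is modest: at 10% the half-width is 5.9 points instead of 5. On the literal reading, the result would fall outside 5–15% about one time in six if the prevalence is 7% (100 − 83.5 = 16.5%).

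These figures rest only on the protocol's inputs and on simple binomial sampling of 100 participants with complete data. They take 7–10% as given and do not judge whether it is realistic.

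**What to change.** Keep 100 participants and delete the claim of 95% certainty for 5–15%. Replace it with the precision the formula gives, for example:

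> With 100 participants, the half-width of the 95% confidence interval for prevalence is 5.0 percentage points if the prevalence is 7% (2–12%) and 5.9 points if it is 10% (4–16%).

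If ±5 points at a prevalence of 10% is to be kept as the target, the protocol's own formula requires 139 participants. Wilson or exact intervals would be sensible for reporting at such low proportions, but that is a recommendation and the correction does not depend on it.

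The cost is one sentence and a slightly less favourable stated precision. No extra participants are needed, and the design and analysis do not change.
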